### Evaluation of the training program

#### Palliative care staff

Assessment of the program will be achieved by using evaluation measures completed by participating staff in the intervention and control groups pre- and post-training, as well as at a three-month follow-up time point (refer to Table 1). As measures of the variables targeted by this intervention have not previously been developed specifically for use in the palliative care context, measures validated in other settings were modified for use in this setting. These were as follows:

1. *Knowledge of depression*. This measure was developed by the research team as a means of assessing palliative care staffs' general knowledge about depression. The questionnaire contains 30 items covering knowledge of the signs and symptoms of depression, facts relating to the impact of depression, and common misconceptions about depression. This scale consisted of items from the *Knowledge of Depression Scale *[21], which has demonstrated good psychometric properties with aged care staff, and items derived from a pool of knowledge-based questions created by the researchers that are specifically relevant to the palliative care setting. These items were informed by the relevant empirical literature and the needs analysis that was conducted prior to program development/modification. An example of an item from this scale is, "Depression is often associated with a hastened desire to die". Responses are measured on a four-point Likert scale ranging from 'strongly disagree' to 'strongly agree'.

2. *Views of depression. *This questionnaire consists of 21 items and will be used to measure staff member's attitudes towards depression and the provision of mental health care. It was constructed from items from a modified version of the *Depression Attitude Questionnaire *[22] and items from a pool of attitude-based questions derived using the same process described above. An example of an item from this scale is, "It is important that carers spend time with patients discussing how they are coping psychologically". Responses are measured on a five-point Likert scale ranging from 'strongly disagree' to 'strongly agree'.

*3. Self-efficacy in detecting and managing depression. *This 16-item questionnaire was adapted to the palliative care setting from a scale originally developed to assess the self-efficacy of care staff in working with depression in the aged care sector [17]. An example of an item from this scale is, "In knowing when it might be time to raise concerns about a patient who might be depressed, I feel...". Responses are measured on a four-point Likert scale ranging from 'not at all confident' to 'very confident'.

4. *Barriers to detecting and managing depression. *This 12-item questionnaire will be used to assess staff members' perceived barriers to detecting depression and providing care for depressed patients and their family members. The items from this scale were constructed from a pool of items created by the researchers and based on the barriers to detection and management of depression identified in the literature review and needs analysis. An example of an item from this scale is, "The stigma associated with depression makes it difficult to talk about such issues with patients and family members". Responses are measured on a four-point Likert scale ranging from 'strongly disagree' to 'strongly agree'.

Semi-structured interviews will be conducted at the three month follow-up with groups of care staff who have participated in the training program to obtain their feedback on the program and how it may have impacted on their practices and level of knowledge, views, self-efficacy and perceived barriers towards working with depression among their patients. These interviews will supplement the data collected in the quantitative measures by gathering more in-depth information and providing a forum for staff to advise on aspects of the training program which they found particularly helpful or informative, aspects that may benefit from further refinement, or by providing other information that may not be captured in the measures. The data collected by both the qualitative and quantitative methods will be used to amend and refine the training program for future delivery to palliative care staff.

#### Patients and their family members

Due to the sensitive nature of research in the palliative care setting no data will be collected directly from patients. Outcomes for patients and their family members will be measured via two methods (refer to Table 1). Firstly, rates of referrals made to specialist health services for depression or suspected depression will be collected at pre-training, post-training, and three-month follow-up points from both the intervention and control facilities. This will allow any increase in patient referrals, compared to the control group, as an effect of staff training to be gauged. Secondly, 30 family members of patients receiving palliative care from the service before and after the training is implemented will be interviewed to determine any perceived changes in staff practices as a result of the training, and the associated outcomes on quality of life for those in their care. A semi-structured approach will be used for these interviews to target areas of potential change whilst also allowing for family members to discuss issues around the provision of depression-related care for their relatives and themselves.

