### Hypotheses and expected outcomes

It is hypothesised that palliative care staff who undertake the depression training program will report higher post-training levels of knowledge, attitudes and self-efficacy and lower perceived barriers in relation to identifying and working with depressed patients compared to pre-training levels and a wait-list control who receive no training. It is also hypothesised that, based on the high prevalence but low detection rates of depression in this context, the number of referrals for depressive symptoms will increase relative to pre-training. The expected outcome of this study is a validated evidence-based program that will assist staff members in recognising depression, increasing appropriate referrals, and improving the care provided for depressed palliative care patients and their family members.

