### Participant groups

A total sample size of 60 was calculated, based on a predicted medium effect size and a statistical power level above 0.8 [16]. Two palliative care services will be recruited into the study with 30 staff from both hospital-based and community based settings recruited from each service. Participants at each site will be randomised to either the intervention condition or the wait-list control condition (no intervention apart from the collection of outcome data). This control group will be offered the training following completion of the study. All attempts will be made to ensure that the sample size and the distribution of participants' professional discipline within the palliative care team (e.g. nursing, occupational therapy, etc.) will be even across sites and conditions.

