### Data analysis

Quantitative and qualitative analysis of the data, and comparison of intervention and control group data, will be used to provide insight into changes in the variables targeted by the interventions, the process of change produced by the targeted intervention, as well as any resulting changes in patient referrals for depression.

The effectiveness of the depression training program will be evaluated using repeated measures multivariate analysis of variance with study condition (intervention or control) as the independent variable and the palliative care staff outcome measures as dependant variables. This type of analysis will facilitate the assessment of changes in staff knowledge, attitudes, self-efficacy and perceived barriers to care for depressed patients and their family members.

All qualitative interviews with staff and family members will be recorded and transcribed. The research team will analyse the interviews to identify and interpret the key themes arising. These themes will be independently identified by members of the research team and cross-checked for inter-rater reliability.

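### Referral rates are to be compared between intervention and control facilities, but staff are randomised within each service, so facility-level rates carry essentially no randomised contrast

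*Protocol article*

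**What the plan says.** Under Participant groups, the Protocol article sets out the layout: "Two palliative care services will be recruited into the study with 30 staff from both hospital-based and community based settings recruited from each service". On allocation it says: "Participants at each site will be randomised to either the intervention condition or the wait-list control condition". Numbers and professional disciplines are meant to be balanced so that they "will be even across sites and conditions", which treats site and condition as crossed factors.

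Under Patients and their family members, referral rates to specialist services for depression "will be collected at pre-training, post-training, and three-month follow-up points from both the intervention and control facilities". The next sentence draws the inference: "This will allow any increase in patient referrals, compared to the control group, as an effect of staff training to be gauged".

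Two other places bear on this. Hypotheses and expected outcomes words the referral hypothesis without a control group: "the number of referrals for depressive symptoms will increase relative to pre-training". Data analysis names one formal method, "repeated measures multivariate analysis of variance with study condition (intervention or control) as the independent variable", with the staff outcome measures as dependent variables. It also mentions comparing intervention and control data in connection with changes in referrals, but names no method for them.

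**The concern.** The two sections disagree about what was allocated. One randomises people inside each service; the other takes for granted that some facilities are intervention and others control. Nothing in the article assigns a facility to a condition, and nothing says that a referral is linked to the staff member who raised it.

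This matters because no data are taken directly from patients. Patient and family outcomes rest on referrals and on semi-structured interviews, so referrals are the only quantitative one. If they are gathered as facility totals, a rise could come from any service-wide change over the period, and the randomisation would not help to separate that from the training.

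**Working it through.** **Inputs** (Participant groups): 2 services; 30 staff per service; 2 conditions; randomisation of participants at each site. The stated total is reproduced as a layout count: 2 × 30 = 60. The power basis of the 60 plays no part here.

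**Reading 1: the randomisation is as described under Participant groups.**

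- Facilities wholly intervention: 0. Facilities wholly control: 0.
- With even allocation, 60 / 2 services / 2 conditions = 15 trained and 15 untrained participants per service.
- Let p₁ and p₂ be the trained shares in the two services, t₁ and t₂ the changes in referrals that would occur without training, and δ₁ and δ₂ the changes if all staff were trained. The facility contrast is then (t₁ − t₂) + (p₁δ₁ − p₂δ₂).
- With p₁ = p₂ = 15/30 = 0.5 and δ₁ = δ₂, the training term is 0.5δ − 0.5δ = 0. Only t₁ − t₂, the difference between services, remains.

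That zero depends on assumptions, so I varied them using figures that are mine and not the article's:

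| Assumed departure | Difference in trained share |
|---|---|
| Even allocation, enrolled staff only | 15/30 − 15/30 = 0 |
| Uneven allocation, 16 trained in one service and 14 in the other | 16/30 − 14/30 = 0.07 |
| Even allocation, but 30 staff able to refer in one service and 60 in the other | 15/30 − 15/60 = 0.25 |

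A true comparison of a fully trained with an untrained facility would have a difference of 1. The contrast is therefore not exactly zero in every case. But where it departs from zero, it does so through chance imbalance or service size, and it stays mixed with t₁ − t₂. In none of these cases is it a comparison of randomised groups.

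**Reading 2: facilities were allocated, one service per condition.** There is 1 facility per arm, and the degrees of freedom for between-facility error are 2 − 2 = 0. Training and service cannot be separated, and the account of randomisation under Participant groups would be wrong.

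**Reading 3: a facility is the hospital or community setting within a service.** Staff come from both settings, but randomisation is of participants at each site and neither setting is tied to a condition. Each setting can again hold both arms, so the conflict remains.

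No reading gives the controlled facility comparison that the article describes.

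**The case against.** The best defence is that facilities is loose wording for groups. The following sentence compares with the control group, not a control facility; Table 1 lists referrals beside the staff measures; and Data analysis speaks of comparing intervention and control data. A journal article condenses the full protocol, which may say how referrals are logged and attributed.

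Part of this stands. A reader might infer that referrals can never be split by condition, and the article does not support that: it is silent on whether the initiator is recorded, and with that link a comparison by condition is possible. A reader might also infer an exact zero or a complete cancellation. That needs an even split, equal effects in both services and equal shares among all staff who can refer. The article promises only an attempt at evenness and does not give the number of referring staff.

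A reader might go further and conclude that the trial's main comparison fails. It does not. The staff questionnaires are compared by randomised condition, and the referral hypothesis, worded against pre-training, can be tested at service level.

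What does not stand is that this is merely an omitted detail. The article states both the source of the data and the inference from it, and both conflict with its own account of randomisation. No later analysis can recover referrals by condition from totals that do not identify who initiated them.

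**Conclusion.** The contradiction is real and lies in current text. Collected as facility-level rates, referrals carry essentially no randomised contrast: the difference in the share of participants trained is close to zero by design if allocation is even. Under the alternative of one service per arm, training is confounded with service. Either way, the statement that a rise over control can be attributed to training is unsupported.

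The core argument needs only that both conditions are present at each site. The 15/15 figure additionally assumes even allocation and counts enrolled staff only. The damage is confined to the controlled, causal reading of referrals.

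**What to change.** Reconcile Participant groups with Patients and their family members, and remove the reference to intervention and control facilities.

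**Where the initiating staff member can be recorded from the pre-training period onward**, suitable text would be: *Each referral, or concern leading to one, is recorded with the study identifier of the staff member who raised it and counted in that person's randomised condition. Referrals per staff member are compared between conditions, adjusted for the pre-training count and site. Whole-service totals are reported alongside.* The totals are needed because a patient referred by a trained carer can no longer be referred by an untrained colleague. Contamination between colleagues who share patients, and referrals with several initiators, should be stated as limits; the linkage does not remove them.

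**Otherwise**, delete the comparison with the control group and the attribution to staff training, and label referrals a descriptive service-level before-after measure. This agrees with the hypothesis as worded and needs no new data.

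Cost: the first option takes logging work before training starts. The article describes no referral log, and if rates come from service records the initiator may not be recoverable. The second option is a text change only, but it gives up the controlled claim on referrals.

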### Data analysis

Quantitative and qualitative analysis of the data, and comparison of intervention and control group data, will be used to provide insight into changes in the variables targeted by the interventions, the process of change produced by the targeted intervention, as well as any resulting changes in patient referrals for depression.

The effectiveness of the depression training program will be evaluated using repeated measures multivariate analysis of variance with study condition (intervention or control) as the independent variable and the palliative care staff outcome measures as dependant variables. This type of analysis will facilitate the assessment of changes in staff knowledge, attitudes, self-efficacy and perceived barriers to care for depressed patients and their family members.

All qualitative interviews with staff and family members will be recorded and transcribed. The research team will analyse the interviews to identify and interpret the key themes arising. These themes will be independently identified by members of the research team and cross-checked for inter-rater reliability.

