## Methods and design

### Intervention design

The study will constitute a randomised controlled trial, implementing a between-subjects repeated measures design to compare intervention and control conditions over four key areas at three time points. The timeline is outlined in Table 1.

**Table 1 T1:** Evaluation timeline for the Depression Training Program

Evaluation measures for assessing outcomes of the "Training program for professional carers to recognise and manage depression in palliative care settings"	Pre-training	Post-training	3 month follow-up
1. Knowledge of depression	✓	✓	✓
2. View of depression	✓	✓	✓
3. Self-efficacy	✓	✓	✓
4. Barriers to working with depression	✓	✓	✓
5. Number of referrals made for depressive symptoms	✓	✓	✓
6. Family member interviews			✓
7. Staff member interviews			✓

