### Consent and Ethics

All participating palliative care staff and patient family members will be provided with a plain language statement and will provide written informed consent to participate in training and/or interviews. Various strategies will be used to maximise the response rate of participating staff members, and participating family members will be offered gift vouchers to compensate for their time. The project has been approved by the Deakin University Human Research Ethics Committee (DU-HREC 2009-194), Eastern Health Research and Ethics Committee (E87/0910) and South West Healthcare Multidisciplinary Ethics Committee (1/2010).

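### The repeated measures MANOVA uses pre-training scores as outcomes and not as covariates, which gives up power that the same 60 staff could provide

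*Protocol article*

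**What the plan says.** The Data analysis section fixes a repeated measures MANOVA "with study condition (intervention or control) as the independent variable and the palliative care staff outcome measures as dependant variables". Condition is the only independent variable named, and no covariate is mentioned.

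The Intervention design section describes a design to "compare intervention and control conditions over four key areas at three time points". Table 1 ticks all four staff measures at each of the three visits. The Palliative care staff section confirms that both arms supply the scores: "evaluation measures completed by participating staff in the intervention and control groups pre- and post-training, as well as at a three-month follow-up time point".

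Under Participant groups, "Participants at each site will be randomised to either the intervention condition or the wait-list control condition", and "A total sample size of 60 was calculated, based on a predicted medium effect size and a statistical power level above 0.8". The Hypotheses section expects trained staff to differ after training both from their own starting level and from the wait-list control.

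The article does not say how missing scores are handled. The nearest text, under Consent and Ethics, is "Various strategies will be used to maximise the response rate of participating staff members".

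**The concern.** With condition as the only independent variable and three repeated occasions, the pre-training score can enter only as an outcome. Staff are randomised, so the expected arm difference at that visit is zero. The score carries no information about the training effect as an outcome, but a good deal as a predictor of the two later scores.

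The time-by-condition test uses it only by subtraction, that is, through change from baseline. Subtraction forces the slope on baseline to be 1, whereas regression adjustment estimates it. Under a common variance and between-visit correlation ρ the best slope is ρ, so subtraction over-corrects whenever ρ is below 1. The price is power in a trial of only 60 people.

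A secondary issue is that repeated measures MANOVA, as usually run, needs a complete set of scores. If the four scales are analysed jointly, that means 4 × 3 = 12 scores per person.

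**Working it through.** **The plan's own figure.** The target is 60 staff, "based on a predicted medium effect size" and "a statistical power level above 0.8". The article does not give the effect metric, alpha, test or correlation, so 60 cannot be uniquely reproduced. An unadjusted comparison of 30 against 30 at one visit, with a standardised difference of 0.5 and two-sided alpha 0.05, has power 0.48. Other readings of a medium effect do exceed 0.8 at 60, for example 0.86 for a one-occasion MANOVA of four outcomes with f² = 0.25. The figure therefore does not settle the matter either way, and the unstated inputs are not the point here.

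**Inputs.** From the article: 60 staff, two arms intended to be even (30 per arm), three visits. Assumed: standardised difference d = 0.5 at both later visits, no expected difference at pre-training, compound symmetry with correlation ρ from 0.3 to 0.8, two-sided alpha 0.05, one measure, complete data, no site term.

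**Step 1, variance at one later visit (SD = 1).**
- Change from baseline: 2(1 − ρ).
- Baseline-adjusted: 1 − ρ².
- Ratio: (1 + ρ)/2, which is 0.65, 0.75 and 0.85 at ρ = 0.3, 0.5 and 0.7. Adjustment removes 35%, 25% and 15% of the variance.

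**Step 2, mean of the two later visits.**
- Mean change: (1 + ρ)/2 + 1 − 2ρ = 1.5(1 − ρ). At ρ = 0.5 this is 0.75.
- Baseline-adjusted mean: (1 + ρ)/2 − ρ². At ρ = 0.5 this is 0.75 − 0.25 = 0.50.

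**Step 3, noncentrality.** λ = (30/2) × 0.5² / variance = 3.75 / variance. At ρ = 0.5 this is 3.75/0.75 = 5.0 for change and 3.75/0.50 = 7.5 after adjustment. Because the effect is equal at both visits, the 2-df tests have the same λ as the 1-df tests and differ only in degrees of freedom.

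**Step 4, power from the noncentral F.** Denominator df are 57 (change) and 56 (adjusted) for the 2-df tests, and 58 and 57 for the 1-df tests.

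| ρ | λ change | λ adjusted | 2-df time-by-condition | 2-df adjusted | 1-df mean change | 1-df adjusted mean |
|---|---|---|---|---|---|---|
| 0.3 | 3.57 | 6.70 | 0.36 | 0.61 | 0.46 | 0.72 |
| 0.5 | 5.00 | 7.50 | 0.48 | 0.66 | 0.59 | 0.77 |
| 0.7 | 8.33 | 10.42 | 0.71 | 0.81 | 0.81 | 0.89 |
| 0.8 | 12.50 | 14.42 | 0.88 | 0.92 | 0.94 | 0.96 |

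**Step 5, sensitivity.**
- Effect halved by three months (0.5, then 0.25), 2-df tests: 0.28 to 0.43, 0.37 to 0.49 and 0.58 to 0.66 at ρ = 0.3, 0.5 and 0.7.
- All four scales jointly (assumed between-scale correlation 0.4, d = 0.5 on each), against a MANCOVA on the four baselines: 0.33 to 0.61, 0.47 to 0.67 and 0.73 to 0.83 at the same ρ.
- If 20% lacked a complete set (assumed; 24 per arm analysed), the 2-df time-by-condition test would have power 0.29, 0.39 and 0.60.

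**The case against.** The planned test is valid. Under randomisation and with complete data the time-by-condition test is unbiased, and a single multivariate test gives some protection against multiplicity across four scales. The gain depends on a correlation that the article does not give, and it is small at about 0.8. All of this stands.

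Several stronger readings are tempting but not supported:

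- A reader might infer that the test is the condition main effect averaged over all three visits, which would dilute a sustained effect to two thirds. The Data analysis section names an independent variable, not a tested effect, and speaks of assessing change. The Hypotheses section points to time-by-condition.
- One might set 0.48 against 0.77 at ρ = 0.5. That compares a 2-df test with a 1-df contrast, so part of the difference comes from changing the contrast. The fair pairs are 0.48 with 0.66, and 0.59 with 0.77.
- One might say that the plan drops everyone with an incomplete set, or that staff who liked the training will return more forms. The first is the usual form of the method and is not stated; a condensed article may leave missing data to the full protocol. If each scale is analysed separately, 3 scores matter and not 12. The second has no support in the text.
- One might conclude that the trial is underpowered. The metric behind the medium effect is not given, so the article alone does not show this.

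**Conclusion.** The point holds as one of efficiency, not validity. Pre-training scores are available on every measure in both arms, and the stated model uses them only as outcomes. Like for like, baseline adjustment adds 10 to 25 percentage points of 2-df power per measure for correlations of 0.3 to 0.7, and about 4 points at 0.8. The direction was the same in every scenario tried, including a fading effect and the joint four-scale test. The size rests on the assumed d = 0.5, compound symmetry and correlation range, none of which the article states. The loss of incomplete cases is secondary and conditional on how the method is run. The change is worth making because it costs little, but the trial is not invalid without it.

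**What to change.** In the Data analysis section, replace the repeated measures MANOVA with one linear mixed model per measure. The outcomes are the post-training and three-month scores. The terms are condition, visit, condition-by-visit, that measure's pre-training score and site. Include all randomised staff with at least one later score, in the arm assigned, and add a rule for a missing pre-training score. Report the adjusted between-arm difference with its 95% confidence interval.

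The cost is a few sentences and standard software, with no new data. There is a small downside: four models replace one joint test. Prespecify one contrast per measure and a multiplicity rule across the four, for example Holm. Alternatively, keep a joint test as a MANCOVA of the later scores on the four baselines; this recovers the efficiency but not the incomplete cases.

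The change has limits that should be stated. Staff with no later score remain excluded, and a likelihood-based model does not remove bias from scores missing not at random.
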